## Abstract

**Background:**

Low health literacy is costly and observed among justice-impacted adults (JIA), a group that often faces numerous barriers in accessing healthcare and a disproportionate burden of illness. Health literacy interventions for JIA are critically needed to improve healthcare access and related outcomes.

**Methods:**

This manuscript describes the protocol for a longitudinal mixed-methods randomized clinical trial that assesses the effectiveness of a coach-guided health literacy intervention on JIA’s healthcare access. The intervention was previously piloted with justice impacted adults. We will recruit 300 JIA ages 18 + in San Diego, California. Participants will be randomized 1:1 to the Treatment Group (i.e., coach-guided intervention providing 12 sessions of individualized health coaching and service navigation over 6 months) or the Control Group (i.e., self-study of the health coaching program, and brief service navigation support). We will quantitatively assess JIA’s healthcare access defined as: use of healthcare, health insurance status, and regular source of care at 6-months as the primary outcomes. Participants will also be surveyed at 12-months. Statistical analyses will incorporate the intent-to-treat (ITT) principle and we will estimate mixed-effects logistic regression for the primary outcomes. We will also conduct qualitative interviews at 6 and 12-months with 40 purposively sampled participants, stratified by study arm, who reported healthcare access barriers at baseline. Interviews will explore participants’ satisfaction with the intervention, healthcare attitudes, self-efficacy for and barriers to healthcare access over time, perceived contribution of the intervention to health and well-being, and diffusion of intervention-related information within participants’ social networks. We will conduct deductive thematic analyses of qualitative data.

**Discussion:**

Low health literacy among JIA is a foundational challenge requiring tailored intervention strategies. Findings from this trial may inform policies and the structure of service delivery models to build health literacy among JIA in institutional and community settings throughout the United States and elsewhere.

**Trial registration:**

This study is registered with the United States’ ClinicalTrials.gov registry under protocol # 161,903.

## Background

The health of justice-impacted adults (JIA; e.g., persons exiting prisons or jails, under community supervision, or in contact with legal systems) can be adversely impacted by multiple factors including low “*personal health literacy*” which refers to the skills that support an individual’s ability to procure, understand, and use resources that support their health and that of other persons (U.S. Department of Health and Human Services, 2023). The need for personal health literacy is high as the adoption of patient-centered care has increased individuals’ responsibilities as healthcare consumers. Patients are expected to draw on visual, quantitative and digital literacy skills in order to use health services properly, communicate effectively with providers, assess risks/benefits of healthcare, and appropriately locate and evaluate information (Kindig et al., 2004; National Institutes of Health Network of the National Library of Medicine, 2020).

While data evaluation the health literacy of JIA are scarce, a small body of qualitative and quantitative studies concur that JIA often face challenges in having the skills (e.g., literacy, numeracy, digital, self-advocacy) or they may encounter barriers to accessing resources (e.g., health information; technology, social support, logistical barriers to healthcare service use) that support health literacy (Donelle & Hall, 2014; Hadden et al., 2018; Mehay et al., 2021; Ramaswamy & Kelly, 2015). Data such as these underscore the need to address multiple intersecting individual and structural conditions in order to support health literacy among JIA.

Addressing health literacy among JIA is important given the higher burden of illness among this sub-group as compared to the general population (Hawks et al., 2020). For example, significant proportions of JIA are impacted by chronic conditions that require regular monitoring and care such as chronic pain (47%), hypertension (34%), asthma (27%), Hepatitis C (24%), arthritis (22%), HIV (14%), and diabetes (13%) (Beckwith et al., 2010; Wang et al., 2012). JIA’s ability to navigate patient-centered care may be complicated by low educational attainment or underdeveloped basic skills (e.g., reading, numeric literacy); moreover, restrictions on self-care in carceral settings may impede development of these skills (Kindig et al., 2004; National Institutes of Health Network of the National Library of Medicine, 2020; Puglisi et al., 2017; Walsh-Felz et al., 2019; Wang et al., 2019). Extant research also finds that low personal health literacy is also associated with reduced use of preventive healthcare, increased use of emergency care, and higher mortality (Berkman et al., 2011; Kindig et al., 2004). Thus, addressing low personal health literacy is a national priority, and strategies tailored to justice impacted adults’ needs are required (U.S. Department of Health and Human Services, 2023).

Two promising strategies that may support JIA and their health literacy include Health Coaching and Service Navigation. Health Coaching is a patient-centered strategy that seeks to build health literacy (Logan et al., 2015) and can be delivered by clinicians or health or peer educators (Ghorob et al., 2013). This approach has been used successfully to help patients manage chronic conditions and improve medication adherence. Health Coaching is associated with improved shared decision-making, information sharing, behavioral changes (Ghorob et al., 2013) and reductions in inpatient and total health care costs (Jonk et al., 2015). Service Navigation may be paired with Health Coaching with the goal of overcoming barriers to services that support well-being (Bernie et al., 2021; Carter et al., 2018; Fox et al., 2014). For example, an estimated 26% of JIA are uninsured (Hawks et al., 2020) and a lack of insurance or a regular source of care can contribute to delaying or forgoing care (Agency for Healthcare Research and Quality, 2018; Hadden et al., 2018). JIA are more likely to utilize emergency care or be hospitalized than the general population (Hawks et al., 2020). JIA also encounter persistent barriers to accessing related services to address the social determinants of health (e.g., employment, housing, nutrition support) and may be challenged when navigating complex systems of care in the community (KUSI Meade & Mellgren, 2011; News, 2020; Patel et al., 2014). Both Health Coaching and Service Navigation can help patients develop or improve executive functioning skills (e.g., goal setting, time management, resource procurement) that are transferrable across diverse settings (e.g., work, school) (Ojeda et al., 2021). Both approaches also provide social support and mentorship and can help individuals build resilience in the face of structural and social challenges (Teggart et al., 2023).

### Pilot study

We first conducted a feasibility study between 2016–2020 in San Diego, California. We piloted a health literacy intervention that jointly implemented Health Coaching and Service Navigation among a sample of adults ages 18–26 under supervision of the local probation department (*n* = 148). The study sought to increase participants’ healthcare utilization (i.e., recent doctor visit, health insurance coverage, having a usual source of care). Participants provided written informed consent to receive 12 weeks of health coaching and up to 6 months of weekly service navigation support. The intervention was delivered in-person; additional service navigation support was provided by phone or text messages if requested (Ojeda et al., 2021). At 6-month follow-up, a subsample of participants (*n* = 66) that were retained until 6-months reported statistically significant improvements in two indicators of healthcare access. Specifically, participants reporting having a doctor visit in the past 6 months increased from 36% at baseline to 71% at 6-months (*p* < 0.001), health insurance coverage increased from 64% at baseline to 88% at 6-months (*p* < 0.01) and the proportion of participants reporting a usual place of care rose from 55 to 70% at 6-months (*p* = 0.09) (Ojeda et al., 2024).

### Study contributions

While thousands of persons interact with the legal system annually, we could not identify any randomized clinical trials (RCTs) in the U.S. that specifically address JIA’s health literacy, highlighting a clear need to develop and test health literacy interventions for this underserved and under-researched community (Puglisi et al., 2017). Despite the increased use of Health Coaching in general populations, to our knowledge, it has not been integrated into healthcare access or health literacy interventions for JIA (Hill et al., 2015) nor has Health Coaching been paired with Service Navigation to support sustained use of healthcare among JIA. This protocol details the procedures for an RCT testing the effectiveness of a novel intervention pairing Health Coaching and Service Navigation to build health literacy with the goal of improving healthcare access among adult JIA ages 18 and older.

## Methods

### Conceptual model

We adapted the systems-level Gelberg-Andersen Behavioral Model of Service Utilization, which has been used to identify factors shaping healthcare use (Aday, 1993; Andersen, 1995; Stein et al., 2007). Key domains of this model include *Predisposing* (i.e., socio-demographics) and *Enabling* factors (e.g., marital status, housing, food security, transportation) which can support healthcare access and maintained use (Aday, 1993; Andersen, 1995; LeBel, 2012). Additional domains include *Need*-related factors (e.g., self-identified health, perceived need for care, clinically evaluated health) and *Health behaviors* including the use of health-promoting activities (e.g., diet, exercise, sleep) (Aday, 1993; Andersen, 1995). These constructs are measured in the baseline and follow-up surveys.

### Study aims & quantitative hypotheses

This study’s primary objective is to assess the effectiveness of a health literacy intervention (i.e., the University of California San Diego Re-Entry Community Linkages [UCSD RELINK] Program) for improving JIA’s healthcare access. Our specific aims for this longitudinal, mixed-methods randomized clinical trial (RCT) are to quantitatively assess the impact of the UCSD RELINK coach-guided health literacy intervention (i.e., health coaching and service navigation) vs. a control group (i.e., self-study of the health coaching program, and brief service navigation support) on healthcare utilization at 6-months and maintenance at 12-months. Secondary quantitative outcomes include assessing health insurance coverage and having a usual source of care. Using qualitative methods, we also seek to understand the impact and maintenance of the intervention at 6 and 12-months.

We hypothesize that participants receiving the coach-guided health literacy intervention will be more likely to report healthcare use at 6 months versus those assigned to the self-study control group. Similarly, we hypothesize that coach-guided health literacy intervention participants will be more likely to report having 1) health insurance and 2) a regular source of care at 6 month follow-up versus control group participants. Maintenance of these outcomes will be assessed quantitatively at 12 months. Additional exploratory outcomes include the types of health services used, type and continuity of health insurance coverage, reasons for being uninsured, delayed care seeking (i.e., has delayed getting medical care in the past 6 months), number of days in hospital, and satisfaction with care.

### Study setting

This study is based in San Diego, California, USA and it is home to > 3.5 million racially and ethnically diverse persons (City of San Diego, 2020). Currently, 35% of the county’s residents are Hispanic, 5.6% are African American, 43% are non-Hispanic White, and 13% are Asian (U.S. Census Bureau, 2023). Local statistics mirror national trends and underscore the disproportionate burden of incarceration on minorities (Carson, 2023). In 2022, local jails detained ~ 4,055 persons/day. During the COVID-19 pandemic, Hispanics and African Americans accounted for 57% of the jail population, but only 39% of the total population (SANDAG, 2023) Persons exiting prison and jail may be supervised by Probation or Parole. For example, in 2023, 42% of local probationers were Hispanic and 23% were African American (vs. 30% White) [total number of probationers > 20,000] (San Diego Probation Department, 2024).

### Ethics & consent

This study was approved by the University of California San Diego Human Subjects Research Protections Program (#161,903). All participants will provide informed consent to enroll in the study. No individual-level data are presented in this manuscript.

### Recruitment & venues

We will use venue-based recruitment to identify eligible individuals at community sites including three local Probation Department field offices, a resource center funded by the District Attorney’s Office, and local employment offices serving JIA.

### Sample & eligibility

This study will enroll 300 persons who meet the following eligibility criteria: is age 18 + , San Diego City resident (i.e., Central, South, Southeast regions), not incarcerated at enrollment, justice-impacted within the last 3 years (i.e., under supervision of probation or parole or court-diverted), available for the duration of the study period, has cell phone access, can provide informed consent, and has conversational English skills. Individuals who participated in the pilot study are ineligible due to prior receipt of the intervention; see ‘Pilot Study’ section, above for details (Ojeda et al., 2021). Adults who have current or prior convictions related to sexual violence/abuse (California Penal Code [PC] 290), lewd acts with a child (PC 288), child abduction (PC 280), or arson (PC 451) are also ineligible due to complications resulting from required interactions with the court and law enforcement agencies that oversee their supervision.

### Orientation & informed consent

Eligible JIA will complete a 90-min orientation led by the study’s recruiter, who will describe the study, answer questions, and obtain informed consent. Participants will complete a locator form and will be randomized to the control or treatment group, described below.

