### *Study arms & randomization*

After being screened for eligibility, participants will be randomized 1:1 to the treatment or control groups, which are described below and summarized in Table 3. A stratified permuted block randomization will be applied to assess the effect of a health literacy intervention (UCSD RELINK) on recent healthcare use among JIA, comparing a coach-guided treatment group versus a self-study control group. A random permutation method with block sizes 4, 6, and 8 will be used where within each block, half the participants will be randomly assigned to the treatment group and the remaining half will be assigned to the control group. We will use data for biological sex at birth to determine which strata an individual will be assigned to (i.e., male or female) before randomizing the participant to an intervention group. Given the small proportion of female JIA, this approach ensures the treatment and control groups will be balanced within biological sex. The randomization list will be generated using Stata v16 (StataCorp., 2019).

**Table 3 Tab3:** Comparison of the UCSD RELINK intervention delivery by study arm

	**TREATMENT GROUP** **Coach-Guided**	**CONTROL GROUP** **Self-Study**
**Program Orientation**	** + **	** + **

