### Treatment arm: coach-guided intervention

Participants randomized to the treatment arm will work with their assigned Health Coach and Service Navigator; sessions are scheduled on days/times that are convenient to staff and participants. Participants will engage with the 12-module health literacy curriculum during weekly sessions with their Health Coach, using the curriculum workbook or program website, per their preference, to facilitate learning and exercise completion. Health Coaches will meet with participants during 12 sessions lasting ~ 45 min throughout a 6-month period. The Health Coach will tailor the curriculum per their needs and interests and guide each participant through the reflection exercises. The curriculum is designed for in-person delivery but can also be implemented by video or phone sessions to ensure continuity of the intervention.

Participants will also receive up to 12 sessions of Service Navigation support, per participant preference, lasting 30-min over a 6-month period. At baseline, the Navigator will conduct the intake survey in order to develop the service navigation plan which identifies resources for participants’ most pressing immediate needs. Navigators and Health Coaches will assist with linkage to resources, goal-setting, and mentoring participants through role-playing and modeling of behaviors that support healthcare access and encourage participants to practice new communication and preventive-care skills in real-world settings (e.g., preparing for healthcare visits, self-advocacy). In partnership with the Health Coach and Service Navigator, participants will reflect on barriers and facilitators and develop personalized solutions to support healthcare service utilization. Participants will also receive a written and electronic emailed Service Navigation report including providers’ contact information for independent follow-up.

Importantly, the intervention adopts a team-based approach: the staff support participants through targeted monitoring meetings to support participant self-management, successes, to anticipate new needs, or exchange resources that may impact their shared work. This approach is influenced by the Collaborative Care Model (CCM); for example, CCM has been successfully used with reentrants for care coordination and service linkages across cross-disciplinary teams (Kim et al., 2019).

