### Control arm: self-study group

Participants assigned to the control arm will work with their assigned Service Navigator for two sessions. During the first session, participants will receive the Health Coaching and Service Navigation workbooks, complete the baseline intake service navigation survey, and will be instructed that they will independently engage with the curriculum using the workbook or the study website (via a personalized log-in which tracks module completion). During the first session, the Service Navigator will assist the participant to establish their study website log-in credentials and how to access the Health Coaching modules on the study website. Participants who prefer to complete the printed curriculum will be instructed to submit photographs of the completed workbook pages to the study email to receive certificates of completion; these may be shared with their supervising officer or the court to demonstrate participation in activities that can benefit the participant reenter the community. During the second study visit, participants will receive a printed and digital (emailed) service navigation report which identifies recommended service providers and resources, including contact information so the participant can access these resources independently. Participants will have opportunities to ask clarifying questions at this visit and no further contact with the Service Navigator will occur.

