### Statistical analyses for survey data

A separate password-protected document with participants’ names and study ID number managed by the database administrator will enable linkage of all surveys. Statistical analyses will incorporate the intent-to-treat (ITT) principle. Participants who are randomized will be included in the ITT population. A mixed-effects logistic regression (Liu, 2015) will be used to analyze the effect of the coach-guided intervention on the primary outcome, recent healthcare utilization (yes/no) over the study period. This approach captures the between-individual and within-individual variability due to the repeated measures. Time invariant covariates include gender and age at baseline in addition to other predisposing, enabling, and health behavior variables determined to be unbalanced at baseline (univariate *p* < 0.10) and associated with the outcome (univariate *p* < 0.15). Time-varying covariates include follow-up time, treatment assignment (intervention vs. control), and time-by-treatment interaction terms. The maximum likelihood estimation approach used in the mixed-effects model enables us to incorporate all participant data even among those with only baseline measures. Analyses will be conducted using Stata v16 (StataCorp., 2019). Methods analogous to the analysis of the primary outcome will be applied to secondary outcome measures: 1) health insurance and 2) a regular source of care. Bonferroni’s correction will be applied for multiple testing of secondary outcomes, so statistical significance will be compared to a *p* < 0.025.

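### The baseline survey follows randomisation and is given by an interventionist, so baseline reports and baseline missingness can depend on the arm

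*Protocol article*

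**What the plan says.** **When allocation happens.** Orientation & informed consent describes a 90-minute visit led by the recruiter, with consent at that visit, and ends: "Participants will complete a locator form and will be randomized to the control or treatment group, described below". No survey is listed before that step. Study arms & randomization names only screening as the preceding step: "After being screened for eligibility, participants will be randomized 1:1 to the treatment or control groups".

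**When the baseline survey happens.** It appears within the arm descriptions.

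- Control: "Participants assigned to the control arm will work with their assigned Service Navigator for two sessions". Then: "During the first session, participants will receive the Health Coaching and Service Navigation workbooks, complete the baseline intake service navigation survey". In the same session these participants "will be instructed that they will independently engage with the curriculum".
- Treatment: "At baseline, the Navigator will conduct the intake survey in order to develop the service navigation plan".

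**Who gives it.** Baseline service navigation intake survey assigns it to Service Navigators in both arms. Interventionist credentials & training counts Navigators among the interventionists.

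**What baseline is used for.** Power & sample size counts it as one of three time points. Statistical analyses for survey data uses a mixed-effects logistic model with time-by-treatment terms, which "enables us to incorporate all participant data even among those with only baseline measures", and admits covariates found unbalanced at baseline (p < 0.10) and associated with the outcome. The qualitative section samples people who reported an access barrier at baseline.

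**The concern.** A baseline value is useful as a reference because the arm cannot have influenced it. Here the participant is likely to know the arm when answering, and the interviewer is the person who will provide the service. The survey is also the intake form for help. A participant offered up to 12 navigation sessions and one offered two may have different reasons to report or play down unmet need.

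Attendance is the second route. Someone who learns the allocation and does not come to the first Navigator session has no baseline, and this can happen more often in one arm.

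A test of change from baseline would absorb either distortion. So would the baseline imbalance screen, which could then react to an effect of allocation and not only to chance. Once participants have been enrolled in this order, no later analysis can recover a clean baseline.

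**Working it through.** **1. Order of steps, from the text.** Screening, orientation, consent, locator form, randomisation, first Navigator session, baseline survey. For control, the last two steps are stated to follow assignment. For treatment, this is inferred: allocation closes orientation, and the survey is then described as work done by the Navigator for participants randomised to that arm. No section describes an outcome measurement before randomisation or a separate assessor.

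**2. The plan's own figures.** The plan gives no figure for baseline attendance or reporting error, so there is none to reproduce on this point. Its sample size is not in dispute. Counting three records per person with an ICC of 0.4, the factor is (1 + 2 × 0.4)/3 = 0.6. At an odds ratio of exactly 1.80 from 40%, 184 × 0.6 = 110.4 per group. At 1.83, which also prints as 1.8, 174 × 0.6 = 104.4, against the plan's 104. Then 208/0.70 = 297.1, consistent with 300. The fix below changes none of this.

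**3. What a reporting shift would do (illustration).** Assumptions: true baseline use is 40% in both arms, control reports it correctly, and treatment reports 40% + d. At 6 months the arms are either equal (odds ratio 1.00) or 60% against 40%, which is (0.60/0.40)/(0.40/0.60) = 2.25.

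Change-from-baseline odds ratio = (6-month odds ratio) / (reported baseline odds ratio).

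For d = −5 points, the reported baseline odds ratio is (0.35/0.65)/(0.40/0.60) = 0.5385/0.6667 = 0.808. This gives 1.00/0.808 = 1.24 and 2.25/0.808 = 2.79.

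| d (points) | Reported baseline OR | No true effect | True 6-month OR 2.25 |
|---|---|---|---|
| −10 | 0.643 | 1.56 | 3.50 |
| −5 | 0.808 | 1.24 | 2.79 |
| +5 | 1.227 | 0.81 | 1.83 |
| +10 | 1.500 | 0.67 | 1.50 |

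These are marginal odds ratios. The subject-specific ratios from the mixed model will differ somewhat. With the same inputs, the between-arm odds ratio at 6 months stays at 1.00 or 2.25 whatever d is, because baseline does not enter it.

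**4. Missing baseline (illustration).** Assume that 5% to 15% of those randomised skip the first session: 300 × 0.05 = 15 and 300 × 0.15 = 45 people without a baseline. Only those who also have no follow-up leave the likelihood. If they are lost at the plan's overall 30%, that is 0.30 × 15 = 4.5 to 0.30 × 45 = 13.5, or about 5 to 14 people. If none of them returns, it is 15 to 45.

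**The case against.** The strongest reply is that the damage is possible but not shown. The same staff role gives the same survey in both arms, in private and for the same $20 card, so a general wish to please the interviewer would be common to both arms. The primary outcome is a yes/no look-back over 6 months, and one session cannot change the past. This stands as a limit on size. It does not remove arm-dependent reporting or selective attendance.

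The second reply also largely stands. The hypothesis in Study aims & quantitative hypotheses is a between-arm comparison at 6 months. In a model with arm-by-time terms, that contrast is the treatment term plus the interaction, which does not subtract baseline. The article does not say which contrast is the primary test.

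Four stronger readings are tempting and are not supported:

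- *Materials are handed out in the survey session in both arms.* This is stated only for control. The treatment text gives no order.
- *A 5-point shift costs a quarter of a planned 20-point effect.* The 5 points are an assumption, the model is logistic, and 60% and 40% are assumed group levels and not changes from baseline.
- *Any shift passes straight into the primary estimate.* That holds only if the interaction alone is the test.
- *The intention-to-treat analysis fails.* The population is defined as everyone randomised, and the plan provides for a CONSORT diagram, reporting of losses and alternative missing-data strategies. Someone who skips the first session but answers later still contributes outcome records, provided the model's covariates are available for that person.

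Blinding is not mentioned in the article. That the Navigator knows the arm is an inference, though a near-certain one given what happens in that session.

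**Conclusion.** The point holds in this form: as written, baseline is collected after randomisation by an interventionist, explicitly in control and by inference in treatment, and the plan then uses it as though it preceded allocation. Baseline reports can be influenced by the arm, and baseline can be missing differentially. Either would bias a change-from-baseline test and disturb the covariate screen. The 6-month between-arm contrast is less exposed. Anyone randomised with neither baseline nor follow-up contributes nothing to the model.

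The size is unknown from the documents. Under the assumptions shown, an arm-specific shift of 5 points moves a null change-from-baseline odds ratio to 1.24 or 0.81. That is material beside a detectable odds ratio of 1.8, but neither the shift nor its direction is evidenced. The case for acting rests on low cost and on the fact that the loss cannot be repaired later, not on a demonstrated bias.

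**What to change.** Set the order as consent, locator form, baseline survey, then allocation, and state that the allocation is generated or revealed only after the survey has been submitted. One workable form is for the Navigator to give the survey at the start of the first visit and open the allocation once it is submitted. The Navigator can then use the completed survey to build the service navigation plan as now. If this is already the practice, correct the orientation, randomisation and control-arm sections to say so.

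The staff role, instrument and sample size stay the same. The cost is about 60 minutes more before allocation (90 + 60 = 150 minutes if done in one sitting with orientation) or a split visit, some rescheduling of Navigators to a stage they do not now cover, and a few $20 cards for people surveyed but not randomised.
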